##### Patient Health Questionnaire (PHQ-9)

2.2.8.2.

The PHQ-9 was developed by Kroenke et al. (2001) and has been adapted and validated for the Portuguese population (Monteiro et al., 2013). The Portuguese version of the PHQ-9 has satisfactory internal consistency (Cronbach’s alpha = 0.86) and showed strong convergent validity with the BDI (*r* = 0.85; *p* < 0.01) (Monteiro et al., 2013). The PHQ-9 consists of nine items that assess the severity of depression-related symptomatology on a 4-point Likert scale (from 0 “Never” to 3 “Nearly every day”). Summed scores range from 0 to 27. Higher scores indicate more severe depression: scores between 0 and 4 indicate minimal depression, scores between 5 and 9 indicate mild depression, scores between 10 and 14 indicate moderate depression, scores between 15 and 19 indicate moderately severe depression, and scores between 20 and 27 indicate severe depression (Kroenke et al., 2001).

##### Metacognitions Questionnaire (MCQ-30)

2.2.8.3.

The MCQ-30 was developed by Wells and Cartwright-Hatton (2004) and is available in Portugese (Dinis and Gouveia, 2011). The questionnaire assesses metacognitive beliefs on five subscales: cognitive confidence, positive beliefs about worry, cognitive self-consciousness, negative beliefs about the uncontrollability of thoughts and danger, and beliefs about the need to control thoughts. The Portuguese version of the MCQ-30 has good internal consistency (Cronbach’s alpha = 0.91; Dinis and Gouveia, 2011). In our study we will apply three subscales of MCQ-30: (1) Positive Beliefs about worry (6 items); (2) Negative Beliefs about thoughts concerning uncontrollability and danger (6 items), and (3) beliefs about the need to control thoughts (6 items). We will only use these three subscales because they are most closely related to depression (Ruiz and Odriozola-González, 2015) and because the remaining two subscales of the MCQ-30, “cognitive confidence” and “cognitive self-awareness,” do not correspond to the concepts of MCT (Jelinek et al., 2013, 2017).

##### Dysfunctional Attitudes Scale (DAS-18B)

2.2.8.4.

The DAS-18B is a self-report questionnaire designed to assess dysfunctional attitudes, thoughts, and schemas associated with depression. It consists of 18 items answered on a seven-point Likert scale (1 = total agreement to 7 = total disagreement). Higher scores indicate more dysfunctional attitudes (Rojas et al., 2015). A methodological study to adapt this instrument to the Portuguese population in an 18-item version will be carried out within the scope of this study.

##### WHOQOL-BREF item 1

2.2.8.5.

The global item (“How would you rate your quality of life?”) of the WHOQOL-Bref (World Health Organization Quality of Life Instruments - Bref) will be used for this study. The WHOQOL-Bref was developed by the WHO in 1998 (The Whoqol Group, 1998) and adapted for the Portuguese population by Vaz Serra et al. (2006).

##### Ruminative Response Scale (ERR-10-A)

2.2.8.6.

This scale is the reduced version (10 items; Treynor et al., 2003) of the Response Styles Questionnaire (RSQ: Response Styles Questionnaire; Nolen-Hoeksema and Morrow, 1991), which was adapted and validated for the Portuguese population (Dinis et al., 2011). This instrument assesses ruminative responses. The ERR-10-A includes 10 items with two factors. The “reflection” factor refers to attempts to understand the reasons for depressed mood (Cronbach’s alpha = 0.75). The “brooding” factor refers to perseverative thinking focused on negative consequences of depressed mood and obstacles to problem-solving (Cronbach’s alpha = 0.76). Respondents are provided with a series of statements referring to “what they usually do when they feel sad depressed or down” and provide answers on a four-point Likert scale, ranging from 1 (‘hardly ever’) to 4 (“almost always”; Dinis et al., 2011).

##### Rosenberg Self-Esteem Scale (RSE)

2.2.8.7.

The Rosenberg Self-Esteem Scale (Rosenberg, 1965) is available in Portuguese (Cronbach’s alpha = 0.86; Santos and Maia, 2003) and is comprised of 10 items concerning self-confidence and self-depreciation. A high score indicates positive feelings that the individual has about himself, leading to self-respect and the awareness that he is capable, without the feeling of superiority. A low score expresses low self-esteem, which implies self-rejection, dissatisfaction, and contempt for oneself (Santos and Maia, 2003).

##### The Attitudes to Ageing Questionnaire – Short form (AAQ-SF)

2.2.8.8.

This instrument was originally created in its 24-item form by Laidlaw et al. (2007) and a short-form (AAQ-SF) was later developed (Laidlaw et al., 2018). The AAQ-SF is a 12-item rating scale and utilizes a 5-point Likert scale. Items query participants’ attitudes regarding aging on three factors (psychosocial loss, psychological growth, physical change). The 12-item AAQ-SF showed adequate internal consistency and confirmatory factor analysis confirmed that the structure of the AAQ-SF reflects that of the original 24-item AAQ (Laidlaw et al., 2018).

##### Intervention questionnaire and patient satisfaction

2.2.8.9.

Assessment of satisfaction with care/treatment should be evaluated in patient-centered approaches (Pinho et al., 2021). The Side Effects of Intervention questionnaire and patient satisfaction with MCT-Silver will be applied to the experimental group post-intervention. To assess the participants’ acceptance of the interventions, a self-designed subjective evaluation scale will be used, consisting of 21 items. This includes 18 items (e.g., “I found the Metacognitive Training programme useful and important”; “I able to cope better with my illness after completing the training”; “The training programme helped me to gain a better understanding of my illness.”) in which participants are asked to respond to the items on a 5-point Likert scale (1 = totally agree; 2 = agree; 3 = neutral; 4 = disagree; 5 = totally disagree). For the interpretation of the evaluation ratings, both positive ratings (i.e., totally agree and agree) are combined for the positively worded items and vice versa for the reversed items. There are also three open-ended items (e.g., “I particularly liked:…”). This information will be useful to understand patient acceptance of and satisfaction with the participants in the study.

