Metacognitive training for older adults with depression (MCT-Silver; Schneider et al., 2018; Bücker, 2019), is a cognitive-behavioral (CBT)-based group intervention, specifically designed for adults ages 60 years and older (all materials are available for free^1^). MCT-Silver aims to reduce the treatment gap by improving access to mental health care for the estimated 73% of older adults with depression who go untreated (Horackova et al., 2019). MCT-Silver is based on metacognitive training for psychosis (MCT; Moritz and Woodward, 2007) and metacognitive training for depression (D-MCT; Jelinek et al., 2015). Randomized controlled trials on D-MCT provide evidence for its efficacy on depressive symptoms (Jelinek et al., 2016), as well as metacognitive and negative cognitive beliefs (Hauschildt et al., 2022; Özgüç and Tanriverdi, 2022) at short- and intermediate follow-up intervals. Long-term efficacy of D-MCT remains equivocal (Jelinek et al., 2019). A pilot study examined the feasibility, acceptance, and effects of D-MCT as an add-on intervention in a group of older adults with depression who were completing an intensive inpatient treatment program (55+ years; *N* = 116). Per protocol analyses (*n* = 55) yielded a significant decrease in depressive symptoms (*d* = 1.06) and cognitive biases (*d* = 0.33). These results support the feasibility and acceptance of D-MCT among older adults with depression. A recently completed RCT in Germany, which compared MCT-Silver to an active control group (cognitive remediation; (Schneider et al., 2018)) yielded large and significant reductions on the primary outcome (Hamilton Depression Rating Scale) from baseline to post and 3-month follow-up (*d_MCT-Silver_* = 1.25 – 1.42; *d*_CR_ = 1.05 – 1.12). Group differences; however, did not reach significance (η_p_^2^ = 0.001 – 0.002). MCT-Silver yielded significant moderate to large effects compared to CR immediately following the intervention and after 3 months for self-reported depression (BDI-II: η_p_^2^ = 0.075 – 0.135) and rumination (RRS: η_p_^2^ = 0.087 – 0.127). A significant moderate effect was found for positive metacognitive beliefs (MCQ-PB) at post-assessment (η_p_^2^ = 0.067), but group differences did not reach significance at follow-up (η_p_^2^ = 0.027). Small reductions in negative cognitive beliefs (Dysfunctional Attitudes Scale-18B) at post- and at 3-month follow-up (*d_MCT-Silver_* = 0.24 – 0.30) were found for the MCT-Silver group, whereas negative cognitive beliefs were unchanged in the CR group (*d_CR_* = –0.06 – 0.06).

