### Aim

2.1.

The aim of this study is to evaluate the efficacy of MCT-Silver and its effects on depressive symptoms, dysfunctional beliefs, metacognitive beliefs, quality of life, ruminative responses, self-esteem and attitudes towards aging. The hypotheses that we want toexamine in this trial are the following:

Primary outcome: There will be a greater reduction in self-reported depression (as measured by the Beck Depression Inventory-II) for MCT-Silver vs. TAU (pre-post; pre-follow-up).Secondary outcomes: There will be a greater reduction in clinician-rated depression (MADRS), metacognitive beliefs (Metacognitions Questionnaire-30), self-reported depression (PHQ-9), dysfunctional beliefs (DAS-18B), ruminative responses (RRS), self-esteem (Self-Esteem Questionnaire), quality of life (WHO QOL-Bref??), and attitudes to aging (Attitudes to Aging Questionnaire) for MCT-Silver vs. TAU (pre-post; pre-follow-up).Tertiary outcome: Participants will rate the intervention positively on a satisfaction questionnaire administered after the 8-week intervention period.

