#### Randomization and blinding

2.2.3.

Eligible participants will be recruited at each institution (the mental health service of each hospital that agreed to take part in the study in Portugal) through telephone contact by the researchers in collaboration with the multidisciplinary team. The study will also be publicized in the media so that older adults can contact the researchers if they are interested in participating. A baseline assessment will be carried out and all instruments will be applied after informed consent from participants. All participants who agree to participate in the study will be assigned a code and will be randomly assigned to either MCT-Silver (experimental group where the intervention will be applied) or the control group (no stratification factors). This randomization will be performed using a computer program. The control group will not be administered the intervention (MCT-Silver). In both groups, treatment will be maintained as usual (Treatment As Usual – TAU) and participation in other interventions as well as use of medications will be carefully monitored. Study participants will be informed that they should not reveal which group they are in and will be reminded of this at each testing session. All participants will be re-assessed at the end of the intervention and 3 months after completion, with the application of all planned instruments. Assessments will be performed by the same rater before and after the intervention and at follow-up. Assessors will be trained in the administration of all instruments prior to the start of the study. A third researcher will inform patients of group assignment so that raters will remain blinded throughout the study. The Side Effects of Intervention questionnaire and patient satisfaction with MCT-Silver will be applied to the experimental group post-intervention (Table 1; Figure 1).

**Table 1 tab1:** Study schedule.

	Study period				
	Enrolment	Randomization	Intervention (8 weekly sessions)	Post (8 weeks)	Follow-up (3 months)
TIMEPOINT	T-1	T0		T1	T2
Enrolment:					
*Eligibility screen*	X				
*Informed consent*		X			
*Randomization*		X			
Interventions:					
*Treatment As Usual (TAU)*	X	X	X	X	X
*MCT-Silver*			X		
Assessments: *Baseline*		X			
*Post-intevention*				X	
*Follow up*					X

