#### Data collection and outcome measures

2.2.6.

The instruments will be administered to all study participants through an interview at three planned assessments (Table 3). To characterize the sample, sociodemographic, and clinical data will be collected [age, sex, marital status, cohabitation, educational level, professional/employment status, duration of depression diagnosis (if applicable), number of psychiatric hospitalizations, medication, type of treatment, and substance use; Table 4]. These data will be collected before the start of the MCT-Silver intervention for all participants.

**Table 3 tab3:** List of study measures and questionnaires.

Instruments	Baseline	8 weeks (post)	3 months (follow-up)
Mini Mental State Examination	X		
Beck’s Depression Inventory (BDI-II)	X	X	X
Patient Health Questionnaire (PHQ-9)	X	X	X
Montgomery-Asberg Depression Rating Scale (MADRS)	X	X	X
Metacognitions Questionnaire (MCQ-30)	X	X	X
Dysfunctional Attitudes Scale (DAS-18B)	X	X	X
WHOQOL-BREF Item 1	X	X	X
Ruminative Response Scale (ERR-10-A)	X	X	X
Rosenberg Self-Esteem Scale	X	X	X
The Attitudes to Ageing Questionnaire (AAQ-12)	X	X	X
Intervention questionnaire and patient satisfaction		X	X

**Table 4 tab4:** Summary of the clinical and demographic characteristics of the sample.

Questions	Answers						
Age							
Gender	Female	Male					
Marital status	Single	Married/ marital partnership	Widowed	Divorced/separated			
Level of education	Cannot read or write	Can read and write, but has not attended school	Attended school, but not higher education	Number of years of schooling	Higher education		
Who you live with	Institution	Alone	Spouse/partner	Child	Brother/sister	Other relative	Other non-family member
Labour status	Employed	Unemployed	Retired	Retired on invalidity	On sick leave	Current or past occupation	
Do you take any medication? If yes, which one?	No	Yes	If so, which one?				
Have you ever been admitted to a psychiatric ward?	No	Yes	How many times?				
Have you ever been to a psychiatric day hospital?	No	Yes	How many times?				
Are you followed up in follow-up appointments/ programmes?	No	Yes	Which ones?				
What is your current substance consumption?	None	Tobacco	Alcohol (more than 3 drinks a day)	Other drugs, which ones?			
Do you have any diagnosed illness(es)?	No	Yes	If so, which one or ones?				

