Minimal negative side effects of D-MCT have been previously reported (Dietrichkeit et al., 2021). We anticipate similar findings, such as disappointment that the training did not result in (greater) symptom improvement and being more burdened by symptoms because patients may think about them more during the training. Attendance (i.e., coming to appointments) may also be perceived as stressful. It is also possible that patients could experience a clinically significance worsening of symptoms. In this case, participation in the study would be discontinued and, if necessary, participants would be offered assistance in identifying needed treatment.

This study includes many measurement instruments and were chosen to improve comparability with previous trails on MCT-Silver and D-MCT (see Jelinek et al., 2015) (Schneider et al., under review, see footnote 3). Nonetheless, completion of study measures can be burdensome and time-intensive for participants. Given that this is the first MCT-Silver trial in Portugal and participants are receiving a psychological intervention, we believe that the potential knowledge to be obtained from the study justifies participants’ time and potential burden related to participation in the study. Additionally, participants are allowed to discontinue testing and will not be penalized for this. Use of self-report measures is common in RCTs of psychological interventions and provide indications regarding patients’ perceptions of symptoms and suffering from these symptoms. Nonetheless, responses are impacted by many factors, including social desirability and insight, as well as reading competence and motivation, which may limit the validity of our findings. For this reason, we have also included a clinician-rated measure of depression (MADRS). The results of the RCT will be implemented to improve the training, provide information regarding efficacy among Portuguese patients (vs. TAU) and, in the case of efficacy, to support dissemination and uptake in Portugal, which would lead to a reduced treatment gap among older adults with depression.

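### Patients who leave the study before 8 weeks, in particular those discontinued for worsening, are not scheduled to be asked about side effects or acceptance, so those results may be too favourable

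*Protocol article*

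**What the plan says.** Acceptance is the article's tertiary outcome. Section 2.1 states the hypothesis: "Participants will rate the intervention positively on a satisfaction questionnaire administered after the 8-week intervention period". Section 2.2.8.9 sets who is asked and when: "The Side Effects of Intervention questionnaire and patient satisfaction with MCT-Silver will be applied to the experimental group post-intervention". Section 2.2.3 repeats this. Table 3 differs: its row "Intervention questionnaire and patient satisfaction" is marked both at 8 weeks and at 3 months.

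The acceptance form is self-designed, with 18 rated and three open items. For interpretation, the two favourable response categories are combined. One of the three rated items given as examples reads "I able to cope better with my illness after completing the training".

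On follow-up, section 2.2.3 says: "All participants will be re-assessed at the end of the intervention and 3 months after completion, with the application of all planned instruments". On leaving, section 2.3 lets participants withdraw whenever they wish. The Discussion says of patients whose symptoms worsen to a clinically significant degree: "In this case, participation in the study would be discontinued and, if necessary, participants would be offered assistance in identifying needed treatment". Neither place mentions asking the patient about side effects or acceptance at that moment.

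**The concern.** A side-effects questionnaire should reach the patients who fared badly. Here the plan has a rule under which some of them leave the study, and it places the questionnaire after the period in which they may leave. Whether a patient is asked can then depend on the very event that the form is meant to pick up. The same applies, less sharply, to acceptance: patients who withdraw because the training disappointed or burdened them would not be asked either.

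At stake are the result for the tertiary hypothesis and the description of side effects, which the Discussion anticipates to be minimal. Answers that were never collected cannot be recovered at the analysis stage. This is therefore a matter of the collection schedule, which the article does fix, and not of analysis detail that may stand in a statistical analysis plan.

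**Working it through.** The article gives no target acceptance rate, no expected dropout and no precision for the tertiary outcome, so there is no figure to reproduce. The check sets the passages side by side and then illustrates the possible size.

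**Step 1. Who is asked?**

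| Situation of a patient allocated to MCT-Silver | Governing text | Scheduled to be asked? |
|---|---|---|
| Attends all sessions and stays in the study | 2.2.3, 2.2.8.9 | Yes, at T1 (and at T2 by Table 3) |
| Stops sessions but stays in the study | 2.2.3 re-assesses all participants; 2.2.9 uses number of sessions attended as a moderator | Yes, as above |
| Discontinued from the study for worsening before T1 | Discussion | No |
| Withdraws from the study before T1 | 2.3 | No |

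The 3-month mark in Table 3 does not help the last two rows, because these patients have left before both visits.

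**Step 2. Item wording.** Of the three example items, one presupposes completion ("I able to cope better with my illness after completing the training"). Another, "I found the Metacognitive Training programme useful and important", can be answered after partial attendance, and so can the third, on understanding one's illness. The other 15 rated items are not shown. The wording problem is therefore shown for one item, not for the form as a whole.

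**Step 3. Possible size for acceptance.** Let d be the share of the MCT-Silver arm that does not answer, pR the share positive among respondents and pN the share positive among non-answerers.

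Overstatement = pR − [(1 − d) × pR + d × pN] = d × (pR − pN).

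All three inputs are assumptions, with pR = 80%. Overstatement in percentage points:

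| d | pN = 80% | pN = 60% | pN = 40% | pN = 20% |
|---|---|---|---|---|
| 10% | 0 | 2 | 4 | 6 |
| 20% | 0 | 4 | 8 | 12 |
| 30% | 0 | 6 | 12 | 18 |

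For example, 0.30 × (0.80 − 0.20) = 0.18.

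**Step 4. Worst-case floor.** If every non-answerer is counted as not positive, the all-allocated percentage is (1 − d) × 80%: 72%, 64% and 56% at d = 10%, 20% and 30%. This is a bound, not an estimate.

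For side effects no comparable calculation is offered, because the article does not give that questionnaire's items or scoring.

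**The case against.** The strongest reply is that stopping sessions is not leaving the study. A reader might infer that everyone who stops the training early drops out of the tertiary outcome. The article does not support this: the form goes to the experimental group and not to completers, all participants are re-assessed, and attendance is a moderator, so partial attenders are expected in the assessed sample. This part of the reply stands. It limits the point to patients who leave the study itself before T1.

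Three further stronger readings should be set aside.

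- **That the result is biased upward.** The direction is plausible but not shown. If non-answerers rate the training as respondents do, the bias is zero.
- **That the earlier D-MCT pilot in older adults gives the dropout rate.** The Introduction reports "Per protocol analyses" on 55 of 116 patients (47.4%). That is an analysis set from a different programme, used as an add-on to intensive inpatient treatment. The article does not say why the others were excluded, and belonging to a per-protocol set is not the same as answering a questionnaire.
- **That dissemination in Portugal rests on the acceptance result.** The Discussion makes dissemination conditional on efficacy.

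It can also be said that the denominator and missing-data rules for a descriptive outcome belong in a fuller protocol or analysis plan. That is fair, and the silence of section 2.2.9 on this outcome is not counted as an error here. A full protocol might also provide for an exit form. But the article states when the questionnaires are given, in three places in the text and in a table, and none of these covers a patient who leaves before T1.

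**Conclusion.** The concern holds in a limited form. Followed as written, the plan leaves patients who exit the study before 8 weeks unasked about side effects and acceptance, and one of the stated routes of exit is clinically significant worsening. The results may therefore be too favourable.

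The size cannot be derived from the article. Under the assumption of 80% positive among respondents and a rating gap of 0 to 60 points, the overstatement of acceptance runs from 0 to 18 points at 10% to 30% non-response. How many patients this affects depends on how often worsening or withdrawal occurs before T1, which the article does not say. A patient whose worsening is first recognised at T1 could still answer there.

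Separately, and without any assumption, the text (post-intervention) and Table 3 (post-intervention and 3 months) disagree on when the form is given, and they must be reconciled.

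The primary and secondary comparisons are not affected.

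**What to change.** 1. Offer the existing side-effects and satisfaction form to every patient allocated to MCT-Silver who leaves the study, at the time of leaving, and to all others at T1. This changes only when the form is offered, not the rule on discontinuation, and answering remains voluntary.
2. Give the completion-dependent items a variant that someone who did not finish can answer. The form is the investigators' own, so this is a wording change.
3. Report the number answering out of all allocated to MCT-Silver beside each percentage among respondents. Show the all-allocated percentage, with non-response counted as not positive, only as a worst-case bound. As a headline it would understate acceptance whenever any non-answerer was satisfied.
4. Reconcile Table 3 with sections 2.1, 2.2.3 and 2.2.8.9, and name one time point for the tertiary hypothesis.

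The cost is a protocol clarification, a variant of an existing form and an extra column in the acceptance table. There are two drawbacks. Exit forms will be completed after differing amounts of training, so they should be identifiable in the report. The acceptance figure may also turn out less favourable.
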